### Statistical analysis

The minimum sample size is estimated on the basis of intubation success rate. Based on previous reports of a 85.3% intubation success rate using the Macintosh laryngoscope with the patient in the lateral position [2] and a 97% intubation success rate using the flexible video endoscope with the patient in the lateral position [7], assuming that 10% of participants would drop out, 87 patients would be required in each group to detect such a difference with a significance level of 5% and power of 80%. PASS 11 (NCSS, LLC; Kaysville, UT, USA) was used for the sample size calculation. Demographic data will be compared using Student’s *t* test. Time to intubation and overall user satisfaction score will be analyzed using the Mann–Whitney U test. Comparison of various rates will be performed using the chi square (χ^2^) test with Yates correction or Fisher’s exact probability test. A *P* value <0.05 is considered statistically significant.

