## Methods

The study will be conducted at the First Affiliated Hospital of Fujian Medical University (Chinese Clinical Trial Register, ChiCTR- IOR-15007175). The study protocol was prospectively approved by the First Affiliated Hospital of Fujian Medical University Ethics Committee.

One hundred and seventy-four patients with American Society of Anesthesiology (ASA) physical status I–II, aged 18–65 years old, who are scheduled for elective kidney surgery in the lateral decubitus position and require endotracheal intubation for general anesthesia will be enrolled in this study. Patients with a body mass index (BMI) > 30 kg/m^2^, cervical spine abnormality, pharyngolaryngeal disorder, anticipated difficult-to-intubate airway, or increased risk of aspiration will be excluded.

Randomization will be performed using computer-generated random numbers, with group and number assignment being stored in sealed envelopes. An envelope will be drawn in the presence of other staff immediately before the patient enters the operating room. Patients will be randomly assigned into two groups to receive flexible video endoscope intubation (FEI) or Macintosh laryngoscope intubation (MLI). Patients within each group will also be randomized to receive intubation in the left or right lateral decubitus position. Figure 1 shows the flow of the patients through the study.

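### 87 patients per group do not give the stated 80% power: with the planned 10% dropout and the tests named, two-sided power is about 67%

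*Protocol article*

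**What the plan says.** The Study outcomes section makes intubation success rate the primary outcome, and the Discussion limits it to the first attempt. The Statistical analysis section sizes the trial on it: "The minimum sample size is estimated on the basis of intubation success rate". The assumed rates are "85.3% intubation success rate using the Macintosh laryngoscope with the patient in the lateral position" and "a 97% intubation success rate using the flexible video endoscope with the patient in the lateral position". With 5% significance and 80% power, the result is: "assuming that 10% of participants would drop out, 87 patients would be required in each group to detect such a difference". The Methods section enrols the matching total: "One hundred and seventy-four patients with American Society of Anesthesiology (ASA) physical status". PASS 11 is named as the software, but not the test option or whether the test is one- or two-sided.

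The same section says that rates will be compared by a chi-square "test with Yates correction or" Fisher's exact test, at P < 0.05. The hypothesis in the Background is non-directional: the devices are expected to differ in clinical performance.

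**The concern.** One paragraph gives the inputs, the resulting number and the tests, and they do not agree. For a difference of this size, 87 looks low even as a count of analysed patients, yet it is said to include a 10% dropout allowance already. In addition, Yates-corrected and Fisher tests are conservative at these sample sizes and need more patients than the uncorrected chi-square.

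This calculation is the only justification given for enrolling 174 patients. If it is wrong, the trial is more likely than stated to miss the difference it was designed to find, and a non-significant result would be read against a power that the design did not have.

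**Working it through.** **Inputs** (Statistical analysis section): p1 = 0.853, p2 = 0.97, difference d = 0.117, alpha 0.05, power 0.80, dropout 10%, 87 per group, 1:1. Assumption: two-sided, because sidedness is not stated, the hypothesis is non-directional and only P < 0.05 is given. So z = 1.960 for alpha and 0.8416 for power.

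**Step 1. Attempt to reproduce 87.**

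Pooled formula, with p̄ = (0.853 + 0.97)/2 = 0.9115:
- √[2p̄(1 − p̄)] = √0.16134 = 0.4017
- √[p1(1 − p1) + p2(1 − p2)] = √(0.12539 + 0.02910) = √0.15449 = 0.3931
- n = (1.960 × 0.4017 + 0.8416 × 0.3931)² / 0.117² = 1.2500 / 0.013689 = 91.3, so 92

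Unpooled formula: n = (1.960 + 0.8416)² × 0.15449 / 0.013689 = 88.6, so 89.

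Continuity-corrected (pooled): n′ = (n/4) × [1 + √(1 + 4/(n·d))]² = (91.3/4) × (1 + √1.3744)² = 107.7, so 108.

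The table adds the sizes at which exact binomial enumeration first reaches 80% power.

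| Two-sided method | Evaluable per group | Randomised (÷ 0.9) |
|---|---|---|
| Pooled formula | 92 | 103 |
| Unpooled formula | 89 | 99 |
| Continuity-corrected formula | 108 | 120 |
| Arcsine formula | 82 | 92 |
| Exact, Yates | 103 | 115 |
| Exact, Fisher | 99 | 110 |
| Exact, uncorrected chi-square | 85 | 95 |
| Exact, unpooled Z | 82 | 92 |
| Exact, likelihood ratio | 81 | 90 |

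No two-sided method that includes the dropout gives 87. For the pooled, unpooled and continuity-corrected formulas and for both named tests, 87 is too few even before any dropout. For the exact uncorrected chi-square, 87 would be enough only if nobody were lost.

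Two one-sided routes come close:
- The unpooled formula gives (1.645 + 0.8416)² × 0.15449 / 0.013689 = 69.8. With continuity correction this becomes 86.02, so 87, but with no dropout allowance.
- The exact unpooled Z test with continuity correction first reaches 80% at 79 per group, and 79/0.9 = 87.8, so 88; multiplying by 1.1 instead gives 86.9, so 87.

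Neither route shows how 87 was actually obtained.

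**Step 2. Power at the stated size.** 87 × 0.9 = 78.3, so 78 evaluable per group. For each test, power is the sum of the binomial probabilities of all pairs of success counts that the test declares significant at two-sided 5%.

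| Test | 78 per group (10% lost) | 87 per group (none lost) |
|---|---|---|
| Yates | 67.0% | 71.0% |
| Fisher | 67.5% | 74.2% |
| Uncorrected chi-square | 78.2% | 81.5% |
| Pooled normal formula | 73.4% | 78.0% |

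The last row is Φ[(d√n − 1.960 × 0.4017)/0.3931]. At n = 78 this is Φ[(1.0333 − 0.7873)/0.3931] = Φ(0.626) = 73.4%.

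**Step 3. If the test were one-sided at 5%.** At 78 per group, exact power is 76.3% (Yates) and 78.3% (Fisher). With none lost, 87 per group gives 81.8% and 83.0%.

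**The case against.** The strongest reply is that 67% is the bottom of a range. It combines a two-sided test, a Yates or Fisher analysis and the full 10% loss.

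- **Dropout.** The primary outcome is known within about a minute of starting the attempt, the envelope is drawn just before the patient enters the operating room, and slow or esophageal attempts count as failures, not as missing. Real loss may well be far below 10%. This stands, but the 10% is the article's own assumption, and with no loss the named tests still reach only 71.0% and 74.2%.
- **Test.** Yates and Fisher are named for rates in general, and the calculation may have used the uncorrected chi-square, which at 78 per group is only about 2 points short. This also stands as a limit on the size of the error. But no uncorrected test is named for the analysis, and that test would need 95 randomised per group with the stated dropout.
- **Sidedness.** It is not stated, and the Discussion suggests that the endoscope may succeed more often. A one-sided option may explain the 87. It would conflict with the non-directional hypothesis, and at 78 evaluable the named tests would still fall below 80%.

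**Conclusion.** The concern holds. The stated 80% power is not delivered under the article's own assumptions: with 78 evaluable per group and a two-sided Yates or Fisher test it is about 67%, a shortfall of 12 to 13 points. The risk of missing the assumed difference is about 33%, against the 20% stated. Without any dropout the risk is 26% to 29%.

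This rests on the two-sided reading, the named tests and the stated 10% loss. Under an uncorrected chi-square the gap shrinks to about 2 points with dropout and disappears without it. How 87 was reached cannot be settled from the article, and the conclusion does not depend on it.

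**What to change.** Rewrite the sample-size paragraph so that it states:
- whether the test is one- or two-sided;
- the PASS option used for the calculation;
- one primary test for success rate;
- the power that 87 randomised per group delivers under that test, with and without the 10% loss. If Yates or Fisher is kept two-sided, this is about 67% at 78 evaluable and 71% to 74% at 87.

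This costs only rewording and a less favourable power statement, with no added patients.

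There is an optional further step. If the uncorrected chi-square is named as the primary test and every randomised patient is analysed, exact power at 87 per group is 81.5% and the 80% statement becomes true. Because recruitment is under way, that choice would have to be made before outcome data are seen, and be dated and documented. Keeping 80% power with the named tests and the 10% loss would instead need 110 (Fisher) or 115 (Yates) randomised per group.

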### Study outcomes

The primary outcome is the intubation success rate. Secondary outcomes include the intubation time, the anesthesiologist’s evaluation of the ease of the technique (using a visual analog scale (VAS) 0–10 [11]), and perioperative side effects and complications. Frequency of esophageal intubation, lip or dental injury, sore throat, and hoarseness will be recorded by a non-blinded observer. Intubation time will be measured using a stopwatch, and each failed intubation attempt will be recorded as 61 s. Secondary outcomes also include the intubation success rate of the combined use of the Macintosh laryngoscope and flexible video endoscope during the second attempt. The patients will be followed up for 24 h after surgery. 

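### The only tests named for the primary success rate, Yates-corrected chi-square or Fisher's exact, are valid but conservative, and fall short of the stated 80% power even with no dropout

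*Protocol article*

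**What the plan says.** The Study outcomes section names a single binary primary outcome: "The primary outcome is the intubation success rate". The abstract lists intubation time beside it, but the trial is sized on the success rate alone.

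The Statistical analysis section plans for 85.3% success with the Macintosh laryngoscope and 97% with the flexible video endoscope. It takes 87 patients per group, "assuming that 10% of participants would drop out", and designs the comparison "with a significance level of 5% and power of 80"%. One sentence then covers every comparison of proportions: "Comparison of various rates will be performed using the chi square" "test with Yates correction or" Fisher's exact test. No other test is named for the primary outcome. The decision rule is that a P "value <0.05 is considered statistically significant". The article does not state sidedness, or which test the sample size calculation assumed.

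**The concern.** With two independent groups and success rates near 90%, failures are few and the distribution of possible tables is coarse. In that setting both the Yates correction and Fisher's conditional test reject well below their nominal level. The unused part of the 5% is paid for in power. If the loss is large, the stated 80% does not describe the analysis that will be run, and a real difference of the planned size is missed more often than the plan implies.

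The correction is also not forced by small counts. At the planning rates the expected failures per arm under a common rate are 78 × 0.0885 = 6.9 or 87 × 0.0885 = 7.7, both above the conventional threshold of 5.

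**Working it through.** **Inputs, all from the Statistical analysis section.** Success rates 0.853 and 0.97, 5% level, 80% power, 87 per arm, 10% dropout. Evaluable number: 87 × 0.9 = 78.3, so 78 per arm. Pooled planning rate: (0.853 + 0.97)/2 = 0.9115. Two-sided testing is assumed. The hypothesis in the Background is of a difference, without direction.

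**The plan's own figure.** The pooled two-sided formula is

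n = [1.960·√(2·0.9115·0.0885) + 0.842·√(0.853·0.147 + 0.97·0.03)]² / 0.117²
= (0.787 + 0.331)² / 0.01369 = 91.3, so 92 per arm, and 92/0.9 gives 103 with dropout.

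The unpooled formula gives 89 (99 with dropout). The smallest sizes with exact two-sided power of at least 80% are 85 for uncorrected Pearson (95 with dropout), 99 for Fisher (110) and 103 for Yates (115). So 87 is not reproduced once dropout is included. Before dropout it lies close to the requirement of an uncorrected test, and well short of what the two named tests need.

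**Exact power and size.** For each n, take every pair (x₁, x₂) of success counts from 0 to n, mark the pairs that the test rejects, and sum Bin(x₁; n, p₁) × Bin(x₂; n, p₂) over them. Power uses 0.853 and 0.97. Size uses 0.9115 in both arms. The N-1 statistic is Pearson's multiplied by (N−1)/N, where N is the total. Boschloo's test uses Fisher's P as its statistic, with a critical value (0.069 at 78 per arm, 0.065 at 87) that keeps size at or below 5% over all common rates.

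| Test | Power, 78/arm | Power, 87/arm | Size at 0.9115, 78/arm | Size at 0.9115, 87/arm |
|---|---|---|---|---|
| Yates (named) | 67.0% | 71.0% | 2.5% | 2.2% |
| Fisher (named) | 67.5% | 74.2% | 2.6% | 2.8% |
| Boschloo | 73.0% | 78.5% | at most 5% | at most 5% |
| N-1 chi-square | 76.2% | 81.5% | 4.7% | 4.9% |
| Uncorrected Pearson | 78.2% | 81.5% | 5.25% | 4.9% |

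Over common rates of 85.3% to 97%, the N-1 test's size is at most 4.9% at 78 per arm and about 5.0% at 87. Its worst case over all rates is 5.1% and 5.8%.

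**Gains over the named tests.**
- Boschloo at 78: 73.0 − 67.0 = 6.0 points over Yates, 73.0 − 67.5 = 5.5 over Fisher. At 87: 78.5 − 71.0 = 7.5 and 78.5 − 74.2 = 4.3.
- N-1 at 78: 76.2 − 67.0 = 9.2 and 76.2 − 67.5 = 8.7. At 87: 81.5 − 71.0 = 10.5 and 81.5 − 74.2 = 7.3.

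**One table as illustration.** Take 13 against 5 failures, 87 per arm.
- Pearson: 174 × (74·5 − 13·82)² / (156·18·87²) = 174 × 696² / 21,253,752 = 3.966, P = 0.046.
- N-1: 3.966 × 173/174 = 3.943, which still exceeds the critical value of 3.841.
- Yates: 174 × (696 − 87)² / 21,253,752 = 3.036, P = 0.081.
- Fisher: P = 0.079.

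**The case against.** The strongest reply is that nothing here is an error. Both named tests are valid, the 5% level is protected, and the choice between conditional and unconditional tests is a long-standing disagreement. That stands as far as validity goes: the harm is lost power, not false positives. It does not answer the gap between these tests and the 80% that the same paragraph states.

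Four stronger readings are tempting, and the documents do not support them.

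- *That the power comes back for free with an uncorrected test.* At 78 per arm the uncorrected Pearson test has true size 5.25% at the pooled planning rate, so part of its advantage comes from exceeding 5%.
- *That the loss is about 11 points whichever test is used.* Against uncorrected Pearson, both tests lose about 11 points at 78 per arm (11.2 Yates, 10.7 Fisher). At 87 Yates loses 10.5 and Fisher only 7.2. Little attrition is plausible, because envelopes are opened just before the patient enters the operating room and the outcome is settled in one attempt of at most 60 s.
- *That the open choice between Yates and Fisher lets the result be picked afterwards.* At the planning rates the two disagree in 0.5% of trials at 78 per arm and 3.2% at 87, always with Fisher significant and Yates not. Taking the smaller P is therefore just Fisher, whose size never exceeds about 4.0%. The rule for choosing may also stand in a fuller document.
- *That the sample size software assumed a different test.* The article does not say which test it assumed, so a mismatch is not shown.

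Sidedness matters too. If 5% were one-sided, Yates and Fisher would reach 81.8% and 83.0% at 87 per arm, but only 76.3% and 78.3% at 78.

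**Conclusion.** The point holds as a matter of efficiency and of a power statement that the named tests do not meet. With two-sided testing at the planning rates, Yates and Fisher deliver about 67% power with 78 evaluable per arm, and 71.0% and 74.2% with 87, at a true size of about 2.2% to 2.8%. A different test would gain about 4 to 8 points with strict size control, or about 7 to 10 points with the N-1 chi-square.

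The shortfall is not all due to the test. At 78 per arm even uncorrected Pearson reaches only 78.2%, and 87 does not reproduce with dropout included. The conclusion rests on the planning rates being right, on two-sided testing, and on the one sentence about rates governing the primary outcome.

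**What to change.** In the Statistical analysis section, name one primary test for the success rate in place of the general sentence. Either of these would serve:

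- the N-1 chi-square without continuity correction, accepting that its exact size can slightly exceed 5% at some rates (worst case 5.8% over all rates at 87 per arm);
- Boschloo's exact test, if strict size control is wanted, at a cost of about 3 points of power against the N-1 test (76.2 − 73.0 = 3.2 at 78; 81.5 − 78.5 = 3.0 at 87).

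State that the test is two-sided, and give the power that it achieves at 78 evaluable per arm: 76.2% or 73.0% on the planning rates. Fisher's test can remain for the rarer complications.

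The cost is a sentence or two and no additional patients. Recruitment is under way, so the change should be made and dated before any comparison of outcomes by group.

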## Discussion

In this clinical trial, we aim to evaluate the efficacy of intubation using a Macintosh laryngoscope or a flexible video endoscope with the patient in the lateral position. Anatomic distortion of the tongue and other tissues of the upper airway differ in the lateral position and supine positions because of the effect of gravity, which can make direct laryngoscopy and subsequent intubation challenging. In addition, endotracheal intubation using direct laryngoscopy in patients in the lateral decubitus position may be difficult in an unfamiliar posture for anesthesiologists and it may take longer to obtain a favorable view of the glottis. Furthermore, even when a grade 1 or 2 laryngoscopic view is attained, it takes longer to confirm successful intubation because the passage of the tracheal tube through the vocal cords is not observed in some patients.

Although fiberoptic bronchoscopy is an important tool to cope with difficult-to-intubate airways, there are only a few studies [7, 12] wherein endotracheal intubation was performed using fiberoptic bronchoscopes with the patient in the lateral position. Li et al. [7] reported that the tracheal intubation success rate with fiberoptic bronchoscopes was significantly higher in the lateral position (97%) compared with that in the supine position (16%), which was contradictory to the results obtained using the Macintosh laryngoscope. Anesthesia administration with the patient in the supine position causes the patient’s tongue and soft tissues of the throat to sag downwards, which can obstruct the operator’s view and the forward motion of a flexible fiberoptic bronchoscope [13]. A possible reason for high success rates using the fiberoptic bronchoscope in the lateral decubitus position might be alleviation of the obstructive effect in this position [7].

Tracheal intubation using a Macintosh laryngoscope, the blade of which is not configured symmetrically, is considered to be easy with the patient in the left lateral position. The difficulty with patients lying in the right lateral decubitus position is the positioning of the tongue, which (influenced by gravity) has a tendency to slip off the laryngoscope blade while the blade is being inserted from the right side of the tongue and moved centrally upwards, thus necessitating shifting the tongue to the left side [14]. The special construction of flexible video endoscopes means that regardless of the patient’s position, anesthesiologists can maintain the upright position to operate. Anesthesiologists can operate flexibly to reveal the glottis by rotating the flexible video endoscope stem and regulating movement of the endoscope tip, which is different from what is possible using a Macintosh laryngoscope in the lateral position.

Another purpose of this clinical trial is to evaluate the effectiveness of the combined use of the Macintosh laryngoscope and flexible video endoscope in difficult airways. In cases where exposure of the glottis is difficult using a Macintosh laryngoscope in the lateral position, the epiglottis can usually be exposed and provoked. Subsequently, a flexible video endoscope can easily help to locate the epiglottis, guided by a Macintosh laryngoscope; thereafter, movements of the front of the flexible video endoscope can be adjusted to locate and enter the glottis.

Our experimental design has certain potential limitations. First, to ensure patient safety, only one attempt with either a Macintosh laryngoscope or a flexible video endoscope will be conducted. If a second or even a third attempt was allowed, the success rate would be different, as the second or the third attempt can also succeed in some cases. Therefore, in the present study, the success rate of tracheal intubation is the success rate only of the first attempted intubation. Second, to maximize patient safety, failed intubation is defined as an intubation attempt that took > 60 s, according to the definition by McCaul et al. [9]. Third, to ensure that the anesthesiologist is adequately skilled in the operation of endotracheal intubation with the patient in the lateral position, the anaesthetist has to practice on a mannequin until the time of intubation is < 60 s. However, this aspect does not reflect real conditions in hospital.

The structure and mode of operation of the Macintosh laryngoscope and the flexible video endoscope are different; therefore, the use of the flexible video endoscope for tracheal intubation with the patient in the lateral position may result in greater success compared with that using a Macintosh laryngoscope. For patients in whom tracheal intubation is difficult in the lateral position, laryngoscopes can be used to increase the space of the pharynx and expose the epiglottis, and subsequently, tracheal intubation can be performed more easily using the flexible video endoscope because of its flexibility of operation.

In conclusion, in this clinical trial, we aim to evaluate the efficacy of intubation using a Macintosh laryngoscope and a flexible video endoscope with the patient in the lateral position and investigate the feasibility of using both devices in combination, when endotracheal intubation in the lateral position has failed with one device. The results of the trial will improve the success rate of tracheal intubation in the lateral position.

## Trial status

Study subjects are currently being recruited into the trial.

## Abbreviations

ASA: American Society of Anesthesiology
BMI: Body mass index
FEI: Flexible video endoscope intubation
HR: Heart rate
MLI: Macintosh laryngoscope intubation
